#### Sample size calculation for cost of TB care among tuberculosis patients

To estimate the effect of integrating traditional care with modern care on the cost of TB care will be considered. The sample size will be calculated by using the two-sample comparison of proportions formula using STATA version 16. A chi-squared of the two independent samples will be used to calculate the sample size using household catastrophic cost incurred that catastrophic household expenditure of P1 = 40% [38] and assuming that the effect of the intervention on the cost of TB care decreased by 13% in the intervention group as compared to the control, P2 = 27% and using, 95% CI, power of 80%, and a type I error of 0.05, considering 10% non-response rate, the final sample size was 453. Since the study is a multicenter individually randomized trial, design effect will be used. According to the multicenter design effect formula, design effect formula is $$\mathrm{design\ effect}=\frac{\upsigma {e}^{2}}{\sigma {e}^{2}+\sigma {B}^{2}}$$ = 1 − *ρ*. The majority of formulas applied on multicenter design with better accuracy relative difference (ICC lesser than 0.052) for designs including more than 10 centers. Assuming that randomization will be balanced and stratified based on centers that have equal group sizes [37]. Assuming the variation between the centers is 0.05, design effect = 1 – *ρ* = 0.95. Therefore, the final sample size will be calculated as sample size * design effect 453 * 0.95 = 428 (214 in the intervention arm and 214 in the control arm).

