### Sample size determination

#### Sample size for TB diagnosis delay among tuberculosis patients

To estimate the effect of integrating traditional care with modern care on diagnosis delay, the sample size will be calculated using the two-sample comparison of proportions formula in STATA version 16. A chi-squared test with two independent samples will be used to calculate the sample size using diagnosis delay. By considering the previous study conducted in the Amhara region with the proportion of diagnosis delay P1 = 59.9% [24] and by assuming that the effect of the intervention on diagnosis delay decreased by 14% in the intervention group as compared to the control, P2 = 45.9%. By considering the probability of a type 1 error of 0.05, 95% CI, power of 80%, and a 10% non-response rate, the total sample size will be 438. Since the study is a multicenter, individually randomized trial, the design effect will be used. According to the multicenter design effect formula, the design effect formula, the $$\mathrm{design\ effect}=\frac{\upsigma {e}^{2}}{\sigma {e}^{2}+\sigma {B}^{2}}$$ = 1 − *ρ*. The majority of formulas applied to multicenter designs have a better relative accuracy (ICC less than 0.052) for designs including more than 10 centers. Assuming that randomized will be balanced and stratified on centers that have equal group sizes [37], assuming the variation between the centers will be 0.05, the design effect = 1 – *ρ* = 0.95. Therefore, the final sample size is calculated as sample size * design effect; 438 * 0.95 = 416 (208 for each arm).

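### The sample sizes for diagnosis delay and cost are cut by a 0.95 factor that a district-randomised trial cannot use, so 80% power is not delivered; the printed 428 is also a small arithmetic slip (430)

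*Protocol article*

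**What the plan says.** Both calculations stand under Sample size determination in the protocol article.

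- **Diagnosis delay.** The control value is "proportion of diagnosis delay P1 = 59.9"%, against 45.9% with the intervention, at a type I error of 0.05 and 80% power. With "a 10% non-response rate, the total sample size will be 438". The last step is "438 * 0.95 = 416 (208 for each arm").
- **Cost of TB care.** The control value is "catastrophic household expenditure of P1 = 40"%, with "P2 = 27% and using, 95% CI, power of 80%, and a type I error of 0.05". Then, "considering 10% non-response rate, the final sample size was 453". A between-centre value follows ("Assuming the variation between the centers is 0.05"), and the last step is "453 * 0.95 = 428 (214 in the intervention arm and 214 in the control arm").

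Both sections justify the 0.95 as 1 − ρ for a multicentre trial that randomises individuals, balanced and stratified by centre. The sections Study design and participants and Randomization and recruitment describe something else: a parallel-group cluster trial in six districts or town administrations, three allocated to each arm.

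**The concern.** Two things stand out. First, the last multiplication for cost is false as printed. Second, a trial that allocates whole districts has its required sample size reduced by a design effect below 1. Clustering of patients within randomised districts calls for a factor above 1.

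At stake is the power statement. If 80% is carried into the trial report, a null result on delay or cost would be read as evidence from an adequately powered comparison when it was not one. Both are secondary outcomes, so the sizing of the primary outcome is not touched by this point.

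**Working it through.** **Inputs.** Delay: p1 = 0.599, p2 = 0.459. Cost: p1 = 0.40, p2 = 0.27. Type I error 0.05, power 80%, non-response 10%, ρ = 0.05, all from the two sample-size sections. Allocation is 1:1, from Randomization and recruitment. A two-sided test is assumed, because one-sided and continuity-corrected versions do not reproduce the printed figures.

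**Step 1: reproduce the plan.** With p̄ = (p1 + p2)/2,

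n per arm = [1.96·√(2p̄(1 − p̄)) + 0.842·√(p1(1 − p1) + p2(1 − p2))]² / (p1 − p2)²

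- Delay: (1.96 × 0.7059 + 0.842 × 0.6989)² / 0.14² = 198.4, so 199 per arm, 398 in total.
- Cost: (1.96 × 0.6675 + 0.842 × 0.6611)² / 0.13² = 205.7, so 206 per arm, 412 in total.
- Non-response as × 1.1: 437.8 and 453.2. These match the printed 438 and 453.
- × 0.95: 438 × 0.95 = 416.1, which matches 416. 453 × 0.95 = 430.35, which does not match 428.

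So one printed step fails. With no loss, cost power is 81.5% at 428 and 81.7% at 430.

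**Step 2: the non-response allowance.** To retain 398 and 412 after 10% loss, divide by 0.9: 442.2 and 457.8, so 443 and 458. With × 1.1, 10% loss leaves about 394 and 408, and power is 79.7% and 79.6%. This costs 0.3 to 0.4 points.

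**Step 3: the power the final numbers carry, ignoring clustering.**

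Power = Φ{[|p1 − p2|·√n − 1.96·√(2p̄(1 − p̄))] / √(p1(1 − p1) + p2(1 − p2))}, with n per arm.

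| Outcome | Enrolled | After 10% loss | Per arm | Power |
|---|---|---|---|---|
| Delay | 416 | 374.4 | 187.2 | 77.7% |
| Cost | 428 | 385.2 | 192.6 | 77.3% |

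Exact chi-squared power is about 78.9% for delay and 77.2–77.5% for cost.

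**Step 4: the same numbers if the 0.95 credit were valid.** Effective n = n/0.95. Delay: 374.4/0.95 = 394.1, power 79.7%. Cost: 385.2/0.95 = 405.5, power 79.4%. The difference from Step 3 is the effect of the factor.

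**Step 5: with clustering.** Design effect = 1 + (m − 1)·ICC, where m is evaluable patients per cluster. Assumptions: equal cluster sizes and arms, 10% loss, no small-cluster correction. The documents give no district-level ICC for these two outcomes. The range runs from 0.03 (stated for detection rate) to 0.05 (the between-centre value).

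| Clusters | ICC | Delay: design effect, power | Cost: design effect, power |
|---|---|---|---|
| 6 | 0.03 | 2.84, 36.2% | 2.90, 35.4% |
| 6 | 0.05 | 4.07, 26.7% | 4.16, 26.1% |
| 40 | 0.03 | 1.25, 68.1% | 1.26, 67.5% |
| 40 | 0.05 | 1.42, 62.6% | 1.43, 61.9% |

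Here m = 374.4/6 = 62.4 and 385.2/6 = 64.2, or 374.4/40 = 9.4 and 385.2/40 = 9.6. The 40-cluster rows use the count given under Sample size calculation for TB detection rate, although the randomisation section names six units.

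**The case against.** The strongest reply is that the sections are coherent on their own premise. They assume individuals randomised within centres, stratified, with ρ = 0.05. Under that premise removing the between-centre variance makes each patient worth 1/0.95, and power after 10% loss is 79.7% and 79.4%, in effect the stated 80%. This is correct as arithmetic. A reader might therefore infer from the 77–78% figures that power fails even under the individual randomisation these sections assume. The documents do not support that, because the shortfall appears only once the stratification credit is withdrawn. It must be withdrawn here because each district receives a single arm, which leaves no within-district comparison to produce the gain.

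A reader might also infer that the sample sizes in general do not follow from their own inputs, or that the 428 slip and the × 1.1 inflation explain the lost power. Neither holds. The figures 438, 453 and 416 all reproduce. The × 1.1 is itself an inference from the printed totals, and the slip and the inflation each cost under half a point.

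Finally, the clustered figures rest on ICC values that the documents do not give for delay or cost at district level. That stands, and it is why they are shown as a range and as illustrations.

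**Conclusion.** The concern holds in this form. The printed 428 should be 430, a trivial slip. The substantive error is a reducing factor borrowed from individually randomised multicentre trials and applied to a trial that randomises districts. With the factor's credit removed, power after the stated non-response is 77.7% and 77.3% before any allowance for clustering, which is 2.3 and 2.7 points below 80%. Allowing for clustering on the assumptions in Step 5, it is about 26–36% with the six districts the protocol randomises, and about 62–68% if 40 clusters were the randomised units. The exact value depends on an ICC the documents do not supply, so no single figure should be taken as the trial's power. Neither cluster count reaches 80% anywhere in that ICC range.

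**What to change.** In the two sample-size sections:

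1. Remove the 0.95 factor and the statement that individuals are randomised within centres. If the multiplication is kept anywhere as a record, print 430 (215 per arm) in place of 428.
2. Compute any non-response allowance by dividing by 0.9: 398/0.9 gives 443 and 412/0.9 gives 458. These would be the totals under simple individual randomisation only, and should be labelled so.
3. Replace the 80% power statement for delay and cost with the power that 416 and 428 enrolled carry under district randomisation. Show it over a stated ICC range, with the number of randomised units named and the small number of clusters acknowledged.

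The cost is a revision of two paragraphs and a short table. If power is restated in this way, no additional patients are required.

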#### Sample size calculation for TB detection rate

Since the case detection rate will be calculated by considering the WHO estimator for the year 2023 per 100,000 populations. Estimating the number of TB cases for that year will be computed by using total cases in the year/100,100 * total population found in the catchment area multiplied by 100, expressed as a percentage. Therefore, all cases that are confirmed as TB patients in the selected districts will be considered as the final sample size.

The number of clusters involved in the study was determined using the following formula [39]: The number of clusters (*K*) required in each arm for unequal cluster sizes was also determined using the formula [40]: *K* = *n* [1 + ((CoV2 + 1) *m* − 1) ICC]/*m*′], where Cov2 = coefficient of variation of 0.25, effective ICC value of 0.03 for cluster-level ICC value of TB detection rate, *n* = sample size under individual randomization, *m* = average number of individuals found in each cluster was 18. From 40 clusters, with unequal clusters for intervention and control arms, 24 clusters included in the intervention, and 16 clusters in the control arm.

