#### Phase 3: Screening and referral of TB-suspected cases

In this phase, a full-blown intervention will be implemented. Traditional healers will screen their clients for TB using standardized screening tools. All suspected TB cases at traditional healer centers, holy water, and mosques will be referred to the nearby health facilities in the intervention districts. A trained TB focal person will screen and diagnose suspected cases based on the national TB treatment guidelines. The content of the interventions, duration, frequency, and dosages are presented in table 1 in Appendix 1.

The progress and evaluation of the intervention will be assessed quarterly and at 6 months. Regular monthly supervision of the implementation will be done by assigned experts. Intermediate outcomes will be assessed during the third and sixth months of the intervention by trained assessors.

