### Randomization and recruitment

Randomization will be done at the district level. There are thirteen districts and two town administrations. Among a total of districts and town administrations, six districts and/or town administrations in South Gondar Zone will be selected using the random.org software by considering the rule of thumb assumption that covers 40% of districts and town administrations. Thus, the selected districts/town administrations will be assigned to the intervention and control arms with a 1:1 allocation ratio. This means three districts or town administrations will be randomly assigned to the intervention arm, and the other three districts or town administrations will be assigned to the control arm. District or town size will not be considered in the randomization process. All health facilities in the intervention and control arms fulfilling the eligibility criteria will be included in the study. The eligibility criteria for the inclusion and/or exclusion of health facilities will be based on the availability of TB diagnostic and treatment services, including the microscope diagnostic service and DOT programs. Participants will recruit to the study when confirmed they have any form of TB and are registered to the DOT programs. Participants will enter into the trial individually based, and patients will recruit continuously until the desired sample size achieve. Recruitment of participants will be from July 1 to September 30, 2022. The statistician who allocated the intervention and control arms, an expert who assesses the outcomes, participants who will be assigned to intervention and control arms, and healthcare providers who provide TB care will not be aware of who were assigned to the intervention and control arms. The project manager and/or investigators will be unblinded.

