### Outcomes of interest

The study will have three outcomes of interest. The primary outcome is the TB case detection rate. The secondary outcomes of interests are diagnosis delay and costs of TB care. The case detection rate will be expressed as percentage. The diagnosis delay will be defined as the time interval between the onset of symptoms and the confirmation of TB diagnosis, which includes patient delay and health system delay. The cost of TB care will include both direct and indirect costs of the patient for TB care and treatment as collected from the patients themselves and their medical records. Direct costs include out-of-pocket payments for medical services (counseling, drugs, laboratory tests, X-rays, and hospital stays) and non-medical services such as transportation, food, and accommodation costs.

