### Measurements

The case detection rate will be calculated as the number of cases notified divided by the number of cases estimated for that year, expressed as a percentage [41]. The WHO estimator for the year 2022 was 132 per 100,000. Estimating the number of TB cases for that year will be computed by using that year/100,100 * total population of the catchment area. Estimating the number of TB cases for that year will be computed by using total cases in the year/100,100 * total population found in the catchment area multiplied by 100, expressed as a percentage.

Patient costs and their annual incomes collected in Ethiopian birr will be converted to US dollars ($) with an average exchange rate for the dates during which data collection took place. The total costs will be considered the sum of the entire direct and indirect costs of TB illness to patients. Out-of-pocket payment for health care (medical) will be the direct payment made for medical care directly by individuals at the time of service using minus insurance reimbursement. Out-of-pocket costs will be a payment for formal medical services, informal traditional practitioners, clinics, health centers, pharmacies, and hospitals for medical services and products such as diagnosis, treatment, and medicine. Out-of-pocket payment net will be a total out-of-pocket payment (medical and non-medical) minus any reimbursement received for payments made. The direct costs will be calculated by the sum of any payment affected by medical and non-medical costs. The medical costs will be the sum of out-of-pocket payments for TB diagnosis and treatment made by TB patients in a given household buying medicines, payments for diagnostic tests, and net reimbursements. The direct non-medical costs were out-of-pocket payments for transport, accommodation, and food before and during TB diagnosis. An indirect cost is costs incurred as a result of TB healthcare seeking and hospitalization, during the TB episode. The total period of absence (in hours) will be multiplied by the hourly wage rate of the absent worker.

Catastrophic costs due to TB: total costs (indirect and direct combined) exceeding a given threshold of the household’s annual income, here defined as exceeding 20%, as recommended by WHO [42].

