## Discussion

This cluster-randomized controlled trial will test the effectiveness of a strategy that integrates traditional healthcare into the modern healthcare system for the control and prevention of TB in northwest Ethiopia, where nearly 90% of the population seeks care from traditional care systems. Although community TB screening has been conducted by community health extension workers, traditional care centers and spiritual healing centers are not easily accessible for community screening. Thus, the integration of traditional care and modern care will be an effective intervention for improving the prevention and control of TB programs. Our study adds screening suspected patients at the place where people gather together at traditional care and holy water centers for healing. Since more than one-third of TB cases are undiagnosed in our community [13], implementing screening for suspected cases in the holy water and traditional care centers probably improves the number of missed cases in the community. In addition, TB patients are diagnosed lately after the onset of the disease and excess expenditure of household costs. This trial will provide information on the effectiveness of traditional and modern health care integration to improve TB case detection and early diagnosis and treatment as well as to reduce the catastrophic cost of TB.

This study may be difficult to reach people who are referred to a health facility by a traditional healer or religious leader for suspected TB, but who do not have a telephone and cannot go to the health facility to which they were referred for various reasons. The other limitation is the project manager and/or investigators will not be blinded.

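### The primary case detection rate counts cases by place of confirmation but divides by a population figure, with no rule linking the two, so non-resident cases could inflate the intervention arm

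*Protocol article*

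**What the plan says.** Under Outcomes of interest the article states: "The primary outcome is the TB case detection rate". Measurements defines it: "The case detection rate will be calculated as the number of cases notified divided by the number of cases estimated for that year". Appendix 2 repeats this definition.

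**Denominator.** Measurements takes the 2022 WHO figure of 132 per 100,000 and continues: "Estimating the number of TB cases for that year will be computed by using that year/100,100 * total population of the catchment area". The catchment area is not defined.

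**Numerator.** The section on sample size for the detection rate says that "all cases that are confirmed as TB patients in the selected districts will be considered as the final sample size". Randomization and recruitment gives the entry rule: "Participants will recruit to the study when confirmed they have any form of TB and are registered to the DOT programs". Neither passage mentions where the patient lives.

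**Intervention arm.** Phase 3 says: "All suspected TB cases at traditional healer centers, holy water, and mosques will be referred to the nearby health facilities in the intervention districts". The Discussion describes the added element as "screening suspected patients at the place where people gather together at traditional care and holy water centers for healing". Control groups keeps passive case finding by self-referral.

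**Related safeguards.** Phase 4 compares end-line with baseline outcomes between the arms. Data quality assurance plans a buffer zone between intervention and control clusters, aimed at information contamination.

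**The concern.** A detection rate can be read as the share of a population's cases that were found only if numerator and denominator refer to the same population. Here cases qualify by where they are confirmed and registered, while expected cases come from a population count. A person from outside the catchment who is confirmed in a selected district adds to the numerator and nothing to the denominator.

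The route for this differs between arms. The intervention creates a new channel from healer centres, holy-water sites and mosques into facilities in the intervention districts, and it applies to all suspects whatever their home. Control districts have no such channel. Some of a measured rise could then reflect where people were diagnosed, not resident cases that would otherwise have been missed. That error would point the same way as the hypothesised benefit, on the primary outcome, with only three units per arm.

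**Working it through.** The article states no expected detection rate or effect size for this outcome, so there is no planned figure to reproduce. The check asks how far the rate moves if some counted cases lie outside the denominator population.

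**Inputs from the article**
- Zone population: about 2.6 million in 2020 (Study settings).
- Candidate units: 13 districts + 2 town administrations = 15; three per arm (Randomization and recruitment).
- Incidence: 132 per 100,000 (Measurements).

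**Assumptions**
- All units are of average size. The article gives no unit populations.
- True resident detection rate 61%, taken as 100% minus the 39% of Amhara cases that the Background reports as undiagnosed or unreported.
- Non-resident share *v* of counted cases: not given, so varied from 2% to 20%.

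**Expected cases**
- Per unit: 2,600,000 / 15 = 173,333 people; × 132 / 100,000 = 228.8 cases.
- Per arm: 3 × 228.8 = 686.4 cases.
- The printed divisor of 100,100 would give 685.7, a difference that does not matter here.

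**Resident cases counted per arm:** 0.61 × 686.4 = 418.7.

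**Effect per case:** 10 / 686.4 = 1.46 percentage points on the arm's rate for each 10 non-resident cases.

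**Effect by share:** observed rate = 61% / (1 − *v*); non-resident cases = 418.7 / (1 − *v*) − 418.7.

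| *v* | Non-resident cases | Observed rate | Artefact (points) |
|---|---|---|---|
| 2% | 8.5 | 62.2% | +1.2 |
| 5% | 22.0 | 64.2% | +3.2 |
| 10% | 46.5 | 67.8% | +6.8 |
| 20% | 104.7 | 76.2% | +15.2 |

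**What changes the net effect**
- An equal non-resident share in both arms raises both rates and leaves their ratio unchanged.
- Outflow offsets inflow. If 5% of the arm's resident cases are confirmed elsewhere while *v* is 5%, the rate is (0.95 × 418.7 + 22.0) / 686.4 = 61.2%, close to the true 61%.
- If the visitors live in control districts and would otherwise have been counted there, the between-arm error doubles: 20 such cases give 2 × 20 / 686.4 = 5.8 points.

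**Whether the planned safeguards help.** Comparison with baseline removes inflow that is constant over time. The gathering-site channel opens with the intervention, so its inflow is absent at baseline and remains in the difference. The buffer zone is directed at information; it may reduce attendance across a border but does not say how a travelling attender is counted.

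**The case against.** The strongest reply is that the key fact is not in the document. The article says that people gather at these sites, not that they come from other districts, and Phase 3 refers suspects to nearby facilities. It does not describe the denominator population as resident, and the sentence on counting all confirmed cases sits in a sample-size section. How a notified case is assigned to a district might be left to the full protocol. Resident outflow can cancel inflow. A visitor who would otherwise have been missed is also a genuine detection.

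Much of this stands. It rules out saying that the rate is inflated, and it rules out any claimed size. It does not remove the point, because the article does state an inclusion rule: confirmed in the district and registered for treatment. Followed as written, that rule admits non-residents, and only one arm has a new channel that could bring them in.

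A reader might also infer that hospitals in town clusters bias the result toward the intervention. The documents do not support that. Towns can be drawn into either arm and the article assigns hospitals to neither, so such inflow is a possible chance imbalance, and if stable it largely cancels against baseline.

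**Conclusion.** The point holds as a risk of differential bias in the primary outcome. Numerator and denominator are not tied to the same population, and the new referral route exists only in the intervention arm.

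Its actual size is unknown. The illustration of about 1.5 points per 10 non-resident cases, or about 3 to 7 points for a 5 to 10% share, rests on average-sized units, an assumed 61% true rate, inflow in one arm only and no offsetting outflow.

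Three stronger readings should be resisted:
- That visitors do inflate the rate: no section says or quantifies that non-residents attend.
- That 10 cases shift the result by 4.4 points: 10 / 228.8 is the shift in one average unit, whereas the comparison is between arms of three.
- That the error doubles: this needs visitors from control districts who would have been found there. Most other candidate units (9 of 14) are outside the trial.

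**What to change.** In the sample-size section for the detection rate, in Measurements and in Appendix 2:

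- Define the catchment population as the residents of the trial district or town administration.
- Record district of residence at registration or in the planned interview.
- Count in the primary numerator only notified cases resident in the district. A resident of another trial district found in any trial facility is credited to the home district; a resident of a non-trial district is left out of the primary count.
- Report non-resident counts by arm and time point, so that any inflow starting with the intervention is visible.
- Keep the place-of-diagnosis rate as a sensitivity analysis.

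Tracing residents diagnosed outside the trial facilities need not be required. It would take registers that the study does not plan to use, so some outflow will stay unmeasured and should be acknowledged.

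The cost is revised wording, one recorded item and some checking of residence. Counts will fall slightly. True extra detections among residents of non-trial districts leave the primary count but remain in the sensitivity analysis.

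### The 40-cluster calculation printed for the TB detection rate does not size that primary outcome: it states no n, control rate, target increase or power, and a count of confirmed patients cannot supply them

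*Protocol article*

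**What the plan says.** All references are to the protocol article.

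- **Outcomes of interest:** "The primary outcome is the TB case detection rate". Diagnosis delay and cost of care are secondary.
- **Measurements:** the rate is notified cases over the year's estimated cases, in percent. It is a population ratio with an estimated denominator.
- **Sample size calculation for TB detection rate**, first paragraph: "all cases that are confirmed as TB patients in the selected districts will be considered as the final sample size".
- **Same section**, second paragraph: a formula for the number of clusters K "required in each arm for unequal cluster sizes was also determined using the formula". Its inputs are a mean cluster size m of 18, an "effective ICC value of 0.03 for cluster-level ICC value of TB detection rate", and a variation term given as "where Cov2 = coefficient of variation of 0.25". The symbol n is defined only as "sample size under individual randomization", with no value. The result is 40 clusters, 24 intervention and 16 control.
- **The two preceding sample-size sections:** for delay, 59.9% against 45.9% at 80% power, where "the total sample size will be 438", reduced to 416 (208 per arm). For catastrophic cost, 40% against 27% at 80% power, total 453, reduced to 428 (214 per arm).
- **Randomization and recruitment:** six districts or towns are randomised, three per arm. Patients enter once TB is confirmed and they are registered for treatment.

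**The concern.** The heading and the label on the ICC both tell a reader that 40 clusters is the size needed for the primary outcome. A sample size for a comparison needs a control value, a difference to detect and a power. None is printed for detection; the only ones in the article belong to delay and cost. The article does not leave the sizing to another document. It prints a formula, inputs and a result, so the question is whether what is printed supports the heading.

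If it does not, the plan makes no supportable statement about what increase in detection the trial can show. A null primary result could then be read as evidence of no effect when the trial could have detected only a very large one.

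**Working it through.** **1. The secondary-outcome totals reproduce.** The check uses the two-proportion formula with pooled variance, two-sided 0.05, 80% power and no continuity correction.
- Delay, 59.9% v 45.9%: 199 per arm, 398 in all; 398 × 1.1 = 437.8, printed 438.
- Cost, 40% v 27%: 206 per arm, 412 in all; 412 × 1.1 = 453.2, printed 453.
- The 0.95 multiplier gives 438 × 0.95 = 416.1 (printed 416) and 453 × 0.95 = 430.4 (printed 428).

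**2. The cluster formula with its own inputs.** K = n[1 + ((CoV² + 1)m − 1)ICC]/m, with m = 18 and ICC = 0.03. The printed divisor carries an undefined prime, which is read here as m.

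Literal reading, CoV² = 0.25: factor = 1 + (1.25 × 18 − 1) × 0.03 = 1 + 21.5 × 0.03 = 1.645.
- Back-solved from the total: n = 40 × 18/1.645 = 437.7.
- Forward from the delay total: 438 × 1.645/18 = 40.03.
- Forward per arm: 208 × 1.645/18 = 19.01 and 214 × 1.645/18 = 19.56. Each rounds up to 20 per arm, 40 in all.

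Other reading, CoV = 0.25, so CoV² = 0.0625: factor = 1 + (1.0625 × 18 − 1) × 0.03 = 1.54375.
- Cost total split by arm: 226.5 × 1.54375/18 = 19.43, so 20 per arm and 40 in all.
- The delay total of 438 gives 37.6.

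Both readings reach 40 from a delay or cost patient number, but not from the same one. An equal requirement of 20 per arm does not explain the 24/16 split, and 16 control clusters fall below it.

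**3. Can any patient-level n size this outcome?** The ratio is notified over estimated cases. Every enrolled patient has confirmed TB, so every one is already detected. Eighteen such patients per cluster contain no undetected cases and give no denominator. The formula treats the data as patient-level responses within clusters; the detection rate is one value per area. The number of randomised areas is six.

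**4. Illustration of what three units per arm can detect.**
- Inputs: three district values per arm, 4 degrees of freedom, two-sided 0.05, 80% power. The noncentral t gives a standardised difference of 3.07.
- Baseline: 61%, from the 39% not reported or not diagnosed in Amhara (Background).
- The between-district coefficient of variation is an assumption; the article gives none for districts.
- Required increase = 3.07 × 61 × CV.

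| Assumed CV | Increase needed (points) |
|---|---|
| 10% | 18.7 |
| 15% | 28.1 |
| 20% | 37.5 |
| 25% | 46.8 |

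For an unadjusted comparison these are lower bounds. They hold the spread at its 61% level and ignore count variation. A second version adds count variation and lets the spread grow with the rate. Its expected cases per district are 2,600,000/15 × 132/100,000 = 228.8, assuming equal-sized units. The rate then needed is about 91% at CV 10% (30 points) and about 124% at CV 20% (63 points).

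**The case against.** **The origin of n is inferred.** A reader might infer from 437.7 against 438 that the delay total was simply relabelled. The article never says so, and the match is not unique. A detection contrast of about 61% v 74% would also need about 199 per arm before non-response, although no such contrast is stated. K is defined per arm, and on that basis both 208 and 214 fit. Rounding matters too: with K = 40 as the total, rounding up admits n from 426.7 to 437.7, which leaves out 438, and rounding to the nearest admits 432.2 to 443.2, which leaves out 428. The damaged formula text also limits how much weight a close match can bear. This part of the objection stands: the source outcome cannot be identified.

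**The variation term.** It is tempting to say that 0.25 was wrongly entered as a square. That does not hold either, because properly squaring it still gives 20 per arm from the cost total of 453.

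**Scope.** The formula is introduced as giving clusters for the study as a whole, and detection is described as a census of confirmed cases. So 40 may have been meant for all outcomes. This is a fair reading, but the section heading and the ICC label still attach the figure to detection, and on this reading the primary outcome has no sizing at all.

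**The illustration.** The between-district variation is assumed, and comparison with or adjustment for baseline, which the article plans, could reduce the required increase. This stands. It is a reason to report the figure both ways, not a reason to leave it out.

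**Conclusion.** The section's heading promises a sample size for the primary outcome, and its content does not provide one. Two things can be read directly and rest on no inference: no n, control rate, target increase or power is given for detection, and a number of confirmed patients per cluster cannot size a ratio of notified to estimated cases. That the inputs fit delay or cost patient numbers is suggestive only.

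The size of the problem can only be illustrated: at least about 19 to 47 points from 61% without baseline adjustment, for an assumed between-district coefficient of variation of 10 to 25%. A reader might go on to infer that the trial cannot succeed because some of these values pass 100%. The documents do not support that. The between-district variation is unknown, baseline adjustment may help, and the denominator is an estimate, so 100% is not a hard ceiling. The defect should be corrected, but it does not by itself invalidate the trial.

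**What to change.** In the section on sample size for the TB detection rate:

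1. Stop presenting the 40-cluster formula as the sizing of the detection rate. State the n it used, the outcome that n came from, whether K is per arm or in total, and whether 0.25 is the coefficient of variation or its square.
2. For the primary outcome, state the smallest increase in case detection rate detectable with three randomised units per arm. Use the between-district variation in the baseline year, before and after adjustment for the baseline rate. An estimate from six units is imprecise, so give a range.
3. Say that conclusions on detection are limited to effects of that size, and that a non-significant result does not exclude smaller ones.

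The cost is a few restated figures from baseline data the trial already plans to collect. No added enrolment is asked for. The downside is that the stated precision for the primary outcome becomes less favourable.
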